### Design

#### Study 1

In Study 1, we want to map the prevalence of psychiatric comorbidity found in the medical records before and after the introduction of The Blue App. The hypothesis is that more diagnoses will be found in the records after the introduction of The Blue App.

#### Study 2

At discharge, eligible patients will be offered participation in a 1-year follow-up study using a randomized controlled design (Figure 1). After receiving informed consent, patients will be randomized into 3 groups and asked to answer questions regarding depressive symptoms (MADRS-S) at different time intervals over a period of 1 year after discharge. The time intervals were chosen to minimize dropout while being long enough to detect effects in the patient. We undertook a power calculation, as we found no comparable studies. Based on estimated scores on the depression rating scale (MADRS-S) at discharge, we expect scores at discharge to be around 30, with SD 7.1.

The null hypothesis for Study 2 is that no significant difference is found in the randomized controlled trial; that is, the feedback given through The Blue App would not improve the outcome or compliance. In the alternative hypothesis, we expect all patients to reduce their MARS-S scores during the study period and expect a difference of about 4 points on MADRS-S between intervention and control groups. With a power of .8, we will therefore need 3 groups of 50 patients each in order to detect differences at a 5% level.

#### Setting and Participants: Studies 1 and 2

Scania in southern Sweden has a population of over 1 million, of which 280,000 are children and adolescents. The university hospital in Malmö, the major city in the area, provides the only psychiatric emergency unit for children and adolescents, with 11 hospital beds. The hospital admits 350 unique patients annually together with a parent for acute stabilization. The most common reasons for admission are suicidal ideations, severely depressed moods, and acute crises. A majority of the patients are aged 13-17 years, with an even gender distribution.

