**Figure 1 figure1:**
[figure not shown]
Study design with 3 randomization groups for the follow-up study at the Child and Adolescent Psychiatric Emergency unit, Malmö, Sweden. ICD-10: International Classification of Diseases, 10th revision; MADRS-S: Montgomery-Åsberg Depression Scale.

Patients and parents will be asked to complete questionnaires on psychiatric symptoms, treatment satisfaction, and quality of life. Included patients will be registered on The Blue App, allowing them to log in via their smartphone using a personal identity number at the log-in page (Figure 2).

The patients will then receive a short message service text message with a one-time password, enabling them to enter The Blue App and answer the questionnaires. It is also possible to generate one-time passwords and complete the questionnaires via The Blue App staff administration view. Parents can use their child’s log-in when answering the parental questionnaires.

The screening process at the unit will be divided into 3 stages (Figure 3). The first stage is defined as the first 24 hours at the unit. The second stage, during treatment, is defined as the time between intake and discharge. The discharge stage is defined as the last 24 hours at the unit. Patients and their parents will be given access to the questionnaires at each stage, which they will complete with the help of staff. At the unit, the questionnaires will be administered mainly on tablets, but can also be filled in via the patients’ own devices.

#### Study 2

At discharge, participation in study 2 will be offered to all patients who complete the questionnaires for Study 1 (Figure 3).

All patients in the study will receive treatment as usual at their outpatient units. Patients will use the same log-in procedure as in Study 1. With app-assisted technology, a link to the MADRS-S questionnaire (Figure 4) will be sent to all participants at predefined intervals depending on randomization.

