### Statistical Analysis

The two studies will be analyzed separately, and baseline variables will be analyzed with descriptive statistics. Pearson’s chi-square tests will be used to determine differences between the groups in terms of gender distribution and proportion of participants scoring above cut-off in the questionnaires used.

In Study 1, we will use descriptive statistics (mean, SD, median, interquartile range, continued variables, frequency and counts, categorical variations, and exact CIs for proportions) to describe the cohort and analyze differences in the number of psychiatric diagnoses before and after the introduction (*t* test) of The Blue App [32].

In Study 2, we will analyze differences between the 3 groups in terms of changes in MADRS-S scores and treatment compliance. Outcome measures (MADRS-S scores and dropout from outpatient care) will be analyzed according to intention to treat. Linear mixed model analyses will be used to identify changes over time in depressive symptoms and to examine compliance with outpatient treatments. In these analyses, group, time, and the intercept between the groups and time will be used as fixed effects and subjects as random intercepts.

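### The Study 2 mixed model has random intercepts only and misnames the group-by-time interaction; type I error may be inflated if patients recover at different rates

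*Protocol article*

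**What the plan says.** The Statistical Analysis section of the protocol article states the aim for Study 2: "we will analyze differences between the 3 groups in terms of changes in MADRS-S scores and treatment compliance". It continues: "Linear mixed model analyses will be used to identify changes over time in depressive symptoms and to examine compliance with outpatient treatments". The model terms are then listed: "group, time, and the intercept between the groups and time will be used as fixed effects and subjects as random intercepts". No random slope, other covariance structure or robust standard error is named.

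The Design section (Study 2) has patients answering MADRS-S "at different time intervals over a period of 1 year after discharge". The Procedure section (Study 2) says that the link to the questionnaire "will be sent to all participants at predefined intervals depending on randomization". On the effect, the Design section says: "we expect all patients to reduce their MARS-S scores during the study period and expect a difference of about 4 points".

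**The concern.** Everyone is expected to improve, so the treatment effect is a difference between groups in change, which is the group-by-time interaction. An intercept between groups and time is not a model term, so the one term that carries the efficacy test is the one misnamed.

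The second issue is the covariance. A random subject intercept implies equal correlation between any two assessments and, within each group, a common slope. The patients are adolescents discharged after a short emergency admission and followed for a year on usual outpatient care. It is plausible, though not documented, that they recover at different rates. If so, slope variation between patients is treated mostly as within-patient noise that averages out over visits. The reported standard error of the interaction is then too small, and the gap grows with the number of assessments.

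**Working it through.** **The plan's own figure.** With a difference of 4, SD 7.1, two-sided 5% and power 0.80: n = 2 × (1.960 + 0.842)² × 7.1² / 4² ≈ 49.5, so 50 per group. Power at 50 is 0.804. The stated 50 per group reproduces and is not in question here.

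**Inputs.** From the Design section: three groups of 50, discharge SD 7.1, 5% level, one year. Assumed, because the readable text does not give them: residual SD σ = 4; slope SD s = 0, 3 or 5 points per year, uncorrelated with the intercept; linear time; m = 2, 3, 5 or 13 equally spaced assessments over the year, the same in all arms. A slope SD of 5 raises the 12-month SD from 7.1 to √(7.1² + 5²) = 8.7, so it is not an extreme value.

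**Formulas.** Let Sxx be the sum of squared deviations of the visit times (in years) from their mean. For one patient's slope:

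- true variance: σ²/Sxx + s²
- variance that the random-intercept model reports: σ²/Sxx + s²/(m − 1), because the slope variance enters the estimated residual variance as s²·Sxx/(m − 1)

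Let r² be the reported variance divided by the true variance. The 2-df Wald statistic for group-by-time is then distributed as χ²₂/r², so a nominal 5% test has actual size 0.05^(r²).

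**Results.**

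| Visits | Sxx | σ²/Sxx | r², s = 3 | Size, s = 3 | r², s = 5 | Size, s = 5 |
|---|---|---|---|---|---|---|
| 2 | 0.500 | 32.0 | 1 | 5.0% | 1 | 5.0% |
| 3 | 0.500 | 32.0 | 36.5/41.0 = 0.890 | 6.9% | 44.5/57.0 = 0.781 | 9.6% |
| 5 | 0.625 | 25.6 | 27.85/34.6 = 0.805 | 9.0% | 31.85/50.6 = 0.629 | 15.2% |
| 13 | 1.264 | 12.66 | 13.41/21.66 = 0.619 | 15.7% | 14.74/37.66 = 0.391 | 31.0% |

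With s = 0, r² = 1 and the size is 5.0% for every schedule.

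**Check by simulation.** REML random-intercept fits to three groups of 50 with no true difference and the same σ rejected in 4.8%, 7.7% and 13.8% of runs at s = 0, 3 and 5 with five visits (1,000 runs each). With thirteen visits they rejected in 13.8% and 31.3% at s = 3 and 5 (400 runs each). This agrees with the formula within simulation error.

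**Unequal schedules.** The intervals depend on the arm, so a single common schedule is a simplification. For one two-arm contrast under a different assumption (intraclass correlation 0.6, s = 4), the size is 8.9% with 5 visits in both arms, 14.9% with 13 in both, and 10.0% with 13 in one arm and 2 in the other.

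**The case against.** A reader might infer that the treatment effect goes untested. The text does not support that. The term follows group and time as main effects, in a paragraph whose aim is between-group differences in change, and the wording makes sense only as *interaction*. The article has other slips, such as the misspelt scale name in the Design section. This part is a one-word correction.

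A reader might also infer that the standard errors are certainly too small. That does not follow either. With no slope variation, or with two assessments in every arm, the test keeps its 5% level. Slope SD, residual SD and visit counts are all assumed here. The schedule may be in Figure 1, which cannot be read, and nothing readable supports thirteen visits in particular.

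Nor does the inflation make a false claim for feedback likely. The sizes above are for a 2-df test across three groups that are exchangeable under the null with a common schedule. The feedback group would have the best slope in about one third of false rejections: about 5% (14/3) to 10% (31/3) even with thirteen visits.

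Finally, random intercepts with group, time and their interaction are a common simple specification, and a fuller analysis plan may exist.

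What remains is that "subjects as random intercepts" is a choice the article makes, not a detail it leaves open. It is a weak choice for a year of repeated measures on arm-dependent schedules.

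**Conclusion.** The point holds in conditional form, with moderate severity. The interaction is misnamed, most likely by a slip. The random-intercept-only structure may inflate the type I error of the group-by-time test if rates of change vary between patients and there are more than two assessments per patient. Under residual SD 4, slope SD 3 to 5 points per year and one schedule in all arms, calculation and simulation together put the size at about 7–10% with three visits, 8–15% with five and 14–31% with thirteen. It stays at 5% with slope SD 0 or two visits. The true size for this trial cannot be fixed from the readable text.

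**What to change.** In the Statistical Analysis section, replace *intercept* with *group-by-time interaction* and name that interaction as the tested effect. Then either add a random slope for time, with Kenward-Roger degrees of freedom, or keep the random intercept and base inference on standard errors clustered by patient.

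An unstructured covariance over common visits should not be relied on: assessment intervals depend on randomization, so the arms need not share visit times.

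The cost is about two sentences before analysis, with no new data and no burden on patients. Confidence intervals widen only as far as slopes really vary. With five visits and intraclass correlation 0.6, the standard error of the one-year difference stays at 1.14 when slope SD is 0 and goes from 1.20 to 1.39 when it is 4. A random-slope model may fail to converge where arms have few assessments; cluster-robust standard errors should be named in advance as the fallback.

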### Limitations

The Blue App has been developed in a Swedish context, which limits its generalizability. Questionnaires are in Swedish, thereby excluding non-Swedish speaking patients. In the next version of The Blue App, the questionnaires will be available in the 4 most common languages at the unit (English, Dhari, Arabic, and French).

The design chosen for Study 2, in which selection is based on participation in Study 1, might affect inclusion and, therefore, could be regarded as a weakness. However, participation in Study 1 gives a thorough assessment of comorbidities at baseline, which is the strength of the design.

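### The Study 2 compliance model uses none of the baseline data collected before randomisation, which gives up some precision

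*Protocol article*

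**What the plan says.** The Procedure section offers Study 2 at discharge only to patients who have completed the Study 1 questionnaires. The Limitations section grants that this selection may be a weakness and sets against it that "participation in Study 1 gives a thorough assessment of comorbidities at baseline, which is the strength of the design".

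The Statistical Analysis section names one linear mixed model for depressive symptoms and for compliance. Group, time and their interaction (printed as intercept) "will be used as fixed effects and subjects as random intercepts". It lists no questionnaire score, diagnosis, age, gender or outpatient unit. Baseline data appear in descriptive summaries and in chi-square comparisons of gender and of the share above questionnaire thresholds. The dropout analysis uses gender, age and main diagnosis.

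Compliance is defined in the Procedure section through outpatient visits kept over the year. On where those visits take place, the article says: "All patients in the study will receive treatment as usual at their outpatient units".

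The Design section sizes the trial on MADRS-S alone. It states "we expect scores at discharge to be around 30, with SD 7.1", and the authors "expect a difference of about 4 points on MADRS-S between intervention and control groups". It concludes: "With a power of .8, we will therefore need 3 groups of 50 patients each".

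**The concern.** The article concedes a selection effect and offers a detailed baseline assessment in return, but the stated model does not use that assessment in the comparison of the groups.

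For compliance the omission has a price. Attendance after discharge has no pre-randomisation value that could act as its own baseline, and its group comparison is made between patients. Comorbidity and functional impairment plausibly predict missed visits, and outpatient units may differ in how often they schedule them. With 50 patients per group, all of that variation stays in the error. The article gives no power figure for compliance, although improving compliance is one of the two aims of Study 2.

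**Working it through.** **1. The article's own figure.** Inputs from the Design section: difference 4, SD 7.1, power 0.80, 5% level (taken as two-sided), 50 per group.

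n per group = 2 × [7.1 × (1.960 + 0.842) / 4]² = 49.46, rounded up to 50.

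Power at 50 = Φ(4 / (7.1 × √(2/50)) − 1.960) = Φ(2.817 − 1.960) = 0.804 (0.797 with the t distribution).

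The stated size reproduces, and it assumes no covariate adjustment.

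**2. Compliance.** Let R² be the share of the variance of a patient's attendance over the year that baseline covariates and unit explain. The article gives no value, so 0.05 to 0.30 is an assumption. In a linear model the standard error of the group difference is multiplied by √(1 − R²). This gives:

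- equivalent gain in patients: 1/(1 − R²) − 1;
- detectable difference at 80% power: 2.802 × √(2/50) × √(1 − R²) = 0.560 × √(1 − R²) SD;
- power for an effect with 0.80 unadjusted: Φ(2.802/√(1 − R²) − 1.960).

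| Assumed R² | Gain in patients | 150 is worth | Detectable difference (SD) | Power |
|---|---|---|---|---|
| 0 | 0% | 150 | 0.560 | 0.80 |
| 0.05 | 5.3% | 158 | 0.546 | 0.82 |
| 0.10 | 11.1% | 167 | 0.532 | 0.84 |
| 0.20 | 25.0% | 188 | 0.501 | 0.88 |
| 0.30 | 42.9% | 214 | 0.469 | 0.92 |

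These gains are before the cost of estimating the covariates. With four of them, the between-patient degrees of freedom fall from 150 − 3 = 147 to 143. The expected loss of precision is of the order 4/147 = 2.7%, so at R² = 0.05 about half the gain is offset.

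**3. MADRS-S change from discharge.** Assume that discharge is a time point in the model, five visits, complete data, total variance 7.1² = 50.41 and intraclass correlation ρ. The standard error of the between-group difference in change is √(2 × 2 × 50.41 × (1 − ρ) / 50). That is 1.68, 1.42 and 1.10 for ρ = 0.3, 0.5 and 0.7. The between-patient variance cancels, so a time-constant covariate entered as a main effect has nothing to remove. Exact generalised least squares standard errors with and without such a covariate had a ratio of 1.000 in every case tried.

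Only the average level over time gains. Its standard error falls by about 4% to 15% when the covariate explains 10% to 30% of the between-patient variance.

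The same reasoning applies to attendance. The gain in step 2 is for the group difference in attendance over the year, not for a group-by-time term.

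**The case against.** The strongest reply is that this is a preference. Randomisation makes the unadjusted comparison valid, a covariate list is normal content for an analysis plan that is not shown, and the article does not say that its listed terms are the only ones. Much of this stands. A reader might infer that the article rules covariates out, but it only lists a model without them. The point survives because the model terms are stated and a better choice is available from data already in hand. It does not rest on silence.

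A reader might also infer that entry was restricted in order to obtain the baseline data. The Limitations section presents them as an advantage that offsets the selection, not as its reason, and it does not promise adjustment. Describing comorbidity in the randomised sample is a legitimate use too.

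The magnitude is hypothetical, since no section relates any baseline variable to attendance. The formula also needs a linear outcome. The article does name a linear mixed model, but the Statistical Analysis section also lists dropout from outpatient care as the compliance outcome. If that is analysed as yes or no, the table does not carry over directly.

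On outpatient units, the text supports only that there is more than one. Their number, the patients per unit, any differences in scheduling and whether the unit is recorded for the study are not given.

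**Conclusion.** The point holds for compliance, as a modest loss of efficiency. Under an assumed R² of 0.05 to 0.30, adjustment is worth about 5% to 43% more patients, or power of 0.82 to 0.92 in place of 0.80. This rests on compliance being analysed linearly as attendance over the year, and on an R² that the documents do not supply.

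Three stronger readings are tempting and are not supported:

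- **The comparison is biased or the sample size is wrong.** The groups are randomised, and 50 per group reproduces from the stated inputs.
- **MADRS-S loses precision in the same way.** For change from discharge with complete data, the subject intercept already removes stable differences between patients. A gain would need discharge to be left out of the outcome vector, levels to be compared, or covariates that act on the slope. The article settles none of these. With missing data, the covariates could make the missing-at-random assumption more credible, if they predict who stops answering.
- **Adjustment costs nothing.** It uses a few degrees of freedom, which matters if R² is near the low end.

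**What to change.** In the compliance model, prespecify a short list of baseline covariates measured before randomisation, for example age, sex, number of conditions positive at screening and the Sheehan Disability Scale. Avoid overlapping items: a separate alcohol or drug indicator may already be counted among the conditions. Add outpatient unit as a random effect if it is recorded and there are enough units to estimate its variance. Report the unadjusted result as a sensitivity analysis.

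In the MADRS-S model the same covariates are optional, and their purpose there is to support the missing-at-random assumption.

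The change is to analysis wording, made before outcome data are examined. It needs no new questionnaires, and because entry requires completed questionnaires, patient-reported covariates should have few missing values. The price is a few degrees of freedom and, for the unit term, confirming that the unit is captured.

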## Results

The app development is described. Data collection for Study 1 started in autumn 2017. Study 2 will be initiated in autumn 2018. We expect to have enrolled 150 patients for Study 2 by December 2019. Funding for both Study 1 and Study 2 have have been granted by Region Skåne, the regional council for health care in south of Sweden. Final results will be published in a scientific journal.

## Discussion

### Principal Findings

This study is a process description of a child and adolescent emergency inpatient unit, where an app was developed with the aim of identifying comorbidity and improving outpatient compliance and treatment outcomes.

### Strengths

The Blue App is a dynamic tool capable of adjustment to new demands, with variable settings, and to other units with potential to improve the transition between inpatient and outpatient care. The Blue App will help us collect data to make it easier to evaluate the work at the inpatient unit and will lay a foundation for future research in the field.

One important factor behind the development process was the support given to the project group from all levels in the organization, from stakeholders to staff [33]. Other crucial factors were related to the project group’s acceptance in the organization and to the committed team members whose perseverance has extended over several years. The organization benefits from the shared visions and team learning [33]. Finally, we want to highlight the importance of being offered enough time to work on this project.

### Limitations

The Blue App has been developed in a Swedish context, which limits its generalizability. Questionnaires are in Swedish, thereby excluding non-Swedish speaking patients. In the next version of The Blue App, the questionnaires will be available in the 4 most common languages at the unit (English, Dhari, Arabic, and French).

The design chosen for Study 2, in which selection is based on participation in Study 1, might affect inclusion and, therefore, could be regarded as a weakness. However, participation in Study 1 gives a thorough assessment of comorbidities at baseline, which is the strength of the design.

### Conclusions

A technically advanced and easy-to-use Web-based mobile phone app corresponding to the unit’s needs was developed, and 2 studies to evaluate its usefulness are planned.

